**Figure 1 F1:**
[figure not shown]
Schematic of data collection in relation to study-specific visits, surgery, and the Active Together assessment pathway. Data will be collected by the Active Together service at baseline, pretreatment and post-treatment, and at 90 days post treatment. Active Together define treatment to include additional forms of acute treatment, for example chemo or radiotherapy, and so pretreatment and post-treatment assessments may occur at varying intervals from surgery. Study-specific data will be collected twice: once as soon as possible after diagnosis, and once within the 2 weeks prior to surgery. Due to differences in treatment pathways and surgery waiting times, the duration between visit 1 and visit 2 will vary between participants, as well as the duration between Active Together assessments. Surgical data will be collected from the surgical team after patient discharge. The study specific, surgical and Active Together outcomes are outlined in the Procedures section.

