### Statistics and analysis

Directed acyclic graphs have been created for the outcome measures in this study to identify confounding factors and determine which variables to adjust for during analysis. Figure 2 shows the causal pathway and potential confounders for investigating the effect of body composition changes on surgical outcomes. Online supplemental material 3 includes directed acyclic graphs for preoperative well-being, post-treatment well-being and 1-year survival. All quantitative data will be treated as continuous data, excluding Clavien-Dindo classification of postoperative surgical complications (ordinal) and the surgical approach, type of surgical complications and treatment pathway (nominal).

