Data from the Active Together service shows that many patients are unable to attend assessment appointments prior to surgery, often due to short notice of surgery dates. This might lead to missing data at the presurgery assessment point (visit 2). All efforts will be made to make attending appointments as convenient as possible for patients. Additionally, patients are routinely weighed before surgery; therefore, the key outcomes of body mass change and surgical outcomes should always be available. Therefore, statistical analyses for body mass change will include all participants, and analyses including body composition, size and shape, and questionnaire data will be performed on a smaller cohort if some data are missing.

Complete case analyses will be performed when covariates (eg, body composition variables) contain missing data. Complete case analysis can lead to biased parameter estimates in regression models if the data are not missing completely at random (MCAR). Therefore, graphical techniques and Little’s hypothesis test of the MCAR assumption will be used to explore whether the MCAR assumption is a reasonable one to make with the collected data. If not, a standard multiple imputation method will be implemented (eg, Multiple Imputation by Chained Equations, Linear Regression Imputation or Predictive Mean Matching).

For linear regression analyses, assuming a medium effect size (F^2^=0.15), significance level=0.05, power=0.8 and number of predictors=6, a sample size of 98 is required.^33^ For correlation, assuming a two-tailed test, a medium effect size (rho=0.3), significance level=0.05 and power=0.8, a sample size of 84 is required.^33^ Therefore, a sample size of 100 participants is required to detect medium effect sizes with acceptable statistical power. Furthermore, 100 participants is a reasonable estimate of the number of potential participants within the study’s time frame based on the demographics of current and previous Active Together patients (ie, number of patients awaiting surgery for upper GI or colorectal cancer with a BMI ≥30 kg/m^2^).

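### The missing-data rules are built around the presurgery visit and missing covariates, so post-treatment and 90-day fitness, nutrition and quality-of-life associations would rest mainly on participants who survive and can attend

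*Protocol article*

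**What the plan says.** **Outcomes.** The Figure 1 legend states: "Data will be collected by the Active Together service at baseline, pretreatment and post-treatment, and at 90 days post treatment". Table 1 lists what the service measures, including the 6-minute walk, 60-second sit-to-stand, handgrip, PG-SGA-SF and EQ-5D-5L. Post-treatment well-being is an analysis target in its own right: the supplement holds "directed acyclic graphs for preoperative well-being, post-treatment well-being and 1-year survival".

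**Missing-data rules** (end of Statistics and analysis):

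- The anticipated gap is visit 2, and the cause given is short notice of the surgery date.
- Patients are weighed routinely before surgery, so "the key outcomes of body mass change and surgical outcomes should always be available". Post-treatment fitness and quality of life are not among the data expected to be complete.
- The default for incomplete data is that "analyses including body composition, size and shape, and questionnaire data will be performed on a smaller cohort if some data are missing".
- A separate rule sets complete-case analysis where a covariate is missing, with body composition as the example. The text accepts that this can bias estimates and plans graphical checks and Little's test of MCAR. It then adds: "If not, a standard multiple imputation method will be implemented".

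The article does not mention outcomes missing after surgery through death, complications or inability to perform a test.

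**The concern.** Before surgery, a short-notice date is a largely administrative reason for missing a visit. After surgery the likely reasons are different. A participant who has died has no assessment. One with severe complications, a long critical-care stay or a readmission is less likely to attend or to manage a walking test. Absence is then a possible consequence of the surgical outcomes that the study relates to body change.

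The Introduction treats muscle loss as linked to complications and mortality. If that holds, absence after surgery lies downstream of the exposure. A model fitted to attenders answers a question about survivors well enough to be assessed. The stated aim concerns patients with gastrointestinal cancer and obesity in the service, and here that means those who had surgery. A weak association with recovery could then partly reflect who is absent.

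**Working it through.** **1. The plan's own figures.** For the regression (f² = 0.15, 6 predictors, alpha 0.05), the overall F test with noncentrality 0.15 × N and N − 7 denominator degrees of freedom gives N = 98 (power 0.804), as stated. For the correlation, ((1.960 + 0.842)/atanh 0.3)² + 3 gives 85 against the stated 84, which is within rounding of method. The plan's rho of 0.3 is the true value below.

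**2. What the rules cover.**

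| Data | Reason for gap considered | Rule |
|---|---|---|
| Body mass change, surgical outcomes | none; expected complete | all participants |
| Body composition, size and shape, questionnaires | missed visit 2 | smaller cohort |
| Covariates | general | complete case, then imputation if MCAR is not reasonable |
| Post-treatment and 90-day questionnaires | none stated | at most the smaller-cohort rule |
| Post-treatment and 90-day fitness tests | none stated | none named |

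**3. Possible size.** The article gives no missingness rate or mechanism, so both are assumed here. The simulation has 2,000,000 participants. Body change X and recovery Y are standard normal, higher is better for both, and the true slope is 0.30. For severity-driven loss, complication severity S lies on the path, with assumed standardised effects X→S = −0.3 and S→Y = −0.5 and a direct effect of 0.15. The total is 0.15 + (−0.3)(−0.5) = 0.30.

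Complete-case slope:

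| Mechanism (assumed) | 5% missing | 10% | 20% |
|---|---|---|---|
| Most severe S lost (sharp) | 0.27 | 0.26 | 0.24 |
| Odds of loss tripled per SD of S (graded) | 0.29 | 0.29 | 0.28 |
| Worst Y lost (sharp) | 0.25 | 0.22 | 0.18 |
| Odds of loss tripled per SD worse Y (graded) | 0.29 | 0.28 | 0.27 |
| Loss depends on X only | 0.30 | 0.30 | 0.30 |
| Loss rises with poor Y and with higher X | 0.33 | 0.34 | 0.37 |

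**4. Scale.** The standard error of the slope is about √((1 − 0.3²)/(n − 2)). At n = 80 this is √(0.91/78) = 0.108. The shift to 0.28 is about 0.02/0.108 = 0.2 standard errors. The shift to 0.18 is about 0.12/0.108 = 1.1.

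**5. Does the remedy work?** Imputing Y from X and S restores 0.30 under both severity-driven mechanisms at all three rates. Under sharp loss of the worst 20% of Y it moves the slope only from 0.18 to 0.20. If the worst 5%, 10% or 20% of outcomes are given a tied lowest rank, Spearman's coefficient is 0.287, 0.286 or 0.283, against 0.287 with full data. That check ranks every missing participant lowest, so it illustrates the principle. It does not test ranking deaths alone.

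**The case against.** **The smaller-cohort sentence closes the visit 2 discussion.** It lists what the study visits collect and does not name fitness tests. This stands: its use for post-treatment questionnaires is a reading of the text, and fitness outcomes have no named rule at all.

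**The plan already has multiple imputation as a fallback.** It may be meant to reach outcomes. If so, the gap narrows but stays open. Imputation would still depend on an MCAR assessment, and nothing says what happens to values that do not exist after death.

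**A condensed article may leave detail to documents not shown.** This is fair for the list of imputation variables and for attendance tables. It is less persuasive for the default itself, because the article states a rule and justifies it with a reason that applies only before surgery.

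**The bias may be small.** Graded loss shifts the slope by a fraction of its standard error, and the larger shifts need sharp selection. This stands. The study is also described as exploratory and disclaims causal inference.

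**Stronger readings to avoid.** A reader might infer that the association is necessarily pulled towards zero. The documents do not support that: attenuation follows if loss depends on recovery or complications, but other mechanisms in the table give no bias or inflation. A reader might also infer that the protocol commits to analysing only survivors well enough to attend. It never says so; that is what the written rules would mostly produce.

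**Conclusion.** The point holds as a gap in rules that were set for a different reason for missingness. As written, the post-treatment and 90-day fitness, nutrition and quality-of-life associations would be estimated mainly in participants who survive and can attend. They may be biased.

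Attenuation is the plausible direction if loss follows complications or poor recovery, but it is not certain. The size cannot be determined from the article. With 20% missing and a true slope of 0.30, the assumed mechanisms that depend on severity or outcome alone give 0.28 to 0.18. One that also depends on body change gives 0.37. All rates, mechanisms and path values are assumptions.

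The change is worth making before analysis. Body mass change and surgical outcomes, which the protocol calls its key outcomes, are not affected by this point.

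**What to change.** For the post-treatment and 90-day fitness, nutrition and quality-of-life outcomes, state a separate rule:

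1. Among operated participants who are alive at the assessment, impute missing outcome values by multiple imputation, whatever Little's test shows. Include Clavien-Dindo grade, critical-care and hospital stay, readmissions, the baseline value of the same measure and body mass change in the imputation model.
2. Do not impute values after death. Report the number of deaths before each assessment and word the main result as conditional on survival.
3. Add a sensitivity analysis that ranks deaths lowest, using the Spearman and ordinal methods already planned.
4. Tabulate attendance at each post-surgery assessment by complication grade.

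**Cost.** The change needs new wording and slightly more analysis, but no new data collection: the auxiliary variables come from hospital records, baseline assessments and preoperative weighing. Intervals may be somewhat wider, and the rank scale in the sensitivity analysis is harder to interpret. Correction is only partial if loss depends on the unobserved outcome itself (0.18 to 0.20 in the sharpest case above), and the report should say so.

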**Methods and analysis:**

This prospective observational study will recruit 100 adults (≥18 years; body mass index ≥30 kg/m²) scheduled for curative upper gastrointestinal or colorectal cancer surgery and enrolled in the Active Together prehabilitation service. Participants will attend two study visits: one as soon as possible after diagnosis and one within 2 weeks before surgery. Participants will undergo body mass, composition and size measurements and complete questionnaires on their nutritional status and quality of life. Routinely collected surgical outcomes (complications, operative approach and duration, length of hospital stay, readmissions, 1-year survival) and Active Together assessment data (physical fitness, psychological well-being, nutritional status) will also be collected. Correlation analyses and regression models will be used to explore the associations between preoperative changes in body mass and composition and surgical, physical fitness, nutritional status and quality of life outcomes.

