### Ethics and dissemination

The Principal Investigator will ensure that this study is conducted in accordance with the principles of the Declaration of Helsinki, relevant regulations and with Good Clinical Practice. This study has been approved by the Health Research Authority (Integrated Research Application System project ID 361634; Research Ethics Committee reference 26/YH/0019). The Principal Investigator will submit and, where necessary, obtain approval from the Health Research Authority for any amendments to the original approved documents.

Prospective participants will be provided with a copy of the Participant Information Sheet which details the nature of the study, what will be required of them, the benefits and risks of their participation and information on how their data will be used. Written informed consent will be provided by all participants at the start of their first visit for the study, before any study-related procedures take place. This will be obtained in the form of a participant-signed and dated informed consent form, including the dated signature of the person obtaining informed consent. The Participant Information Sheet and all other participant-facing documentation has been scrutinised and deemed appropriate by the Public and Patient Involvement steering committee.

A participant may choose to withdraw early from the study at any time. If a participant withdraws from the study before their second visit or surgery, their data will also be removed from the study dataset as both visits and surgical data are required to answer the research questions. If a participant withdraws from the study after their surgery, no further data will be collected from their records (surgical or Active Together outcomes) for the study, but data that has already been collected (ie, from surgery and the two data collection sessions) will be used for analysis. Participants will be made aware of their right to withdraw and what happens to their data on withdrawal via the Participant Information Sheet and give consent to this on the Informed Consent Form.

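### The 80% power claim for the six-predictor regression needs 98 complete cases out of 100 recruited, although the plan itself foresees missing pre-surgery data and deletes early withdrawals

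*Protocol article*

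**What the plan says.** The Statistics and analysis section of the protocol article gives two sample size calculations. For regression: "assuming a medium effect size (F^2^=0.15), significance level=0.05, power=0.8 and number of predictors=6, a sample size of 98 is required". For correlation: "assuming a two-tailed test, a medium effect size (rho=0.3), significance level=0.05 and power=0.8, a sample size of 84 is required". From these it concludes: "Therefore, a sample size of 100 participants is required to detect medium effect sizes with acceptable statistical power". The abstract makes clear that this is a recruitment number: "This prospective observational study will recruit 100 adults".

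The following statements bear on how many of the 100 can be analysed:

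- **Missed assessments.** Statistics and analysis reports, from the service's own data, that "many patients are unable to attend assessment appointments prior to surgery, often due to short notice of surgery dates", and says that visit 2 data might be missing as a result.
- **Analysis sets.** Body mass change is to be analysed in all participants, because patients are routinely weighed before surgery. Composition, size and shape, and questionnaire analyses use a smaller cohort if data are missing. Complete-case analysis is the default, and multiple imputation is used only if data missing completely at random (MCAR) is not a reasonable assumption.
- **Withdrawals.** Ethics and dissemination says of participants who withdraw before their second visit or surgery that "their data will also be removed from the study dataset".
- **Off-site sessions.** Procedures (Primary data) lets participants who cannot travel be measured elsewhere with impedance scales and questionnaires, but without the 3D body scan.
- **Size of the pool.** Statistics and analysis adds that "100 participants is a reasonable estimate of the number of potential participants" within the time frame.

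**The concern.** The sample size statement treats the recruited number as the analysed number. The larger of the two requirements is 98, so the stated power survives the loss of two participants. The same section expects missed assessments at the visit that supplies the second measurement of composition, shape and the questionnaires, and it makes no allowance for them. Nor does it restrict the power claim to the analyses that escape this loss.

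The Introduction rests the study on composition: losing fat may help and losing muscle may harm. Those analyses are the exposed ones. A reader who takes the power statement at face value would credit a non-significant overall regression, or a non-significant correlation, with a sensitivity it may not have. The pool is put at about 100 potential participants, so the documents show little room to recruit more in compensation.

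**Working it through.** **Inputs.** From Statistics and analysis: f² = 0.15, α = 0.05, power 0.80, six predictors, N = 98; rho = 0.3, two-tailed, N = 84; target 100. The loss rate is not in the documents, so 5% to 30% is assumed, with 40% as a further case for the single coefficient.

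**1. Reproducing the plan's figures.** The overall F test of a regression with six predictors has 6 and N − 7 degrees of freedom and noncentrality λ = f² × N.

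- N = 98: λ = 0.15 × 98 = 14.70, power 80.4%.
- N = 97: λ = 0.15 × 97 = 14.55, power 79.8%.

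So 98 is the smallest N that reaches 80%, as stated. For the correlation, the Fisher z approximation gives 85 and simulation of the t test under bivariate normality gives 84 (power 80.2%). Both stated figures stand.

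**2. Allowance in the target.** 100 − 98 = 2 participants (2%) for the regression. 100 − 84 = 16 (16%) for the correlation, or 15 if 85 is used.

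**3. Power by number of complete cases.** The regression column is the overall test at f² = 0.15. The correlation column uses the Fisher z form, Φ(atanh(0.3) × √(N − 3) − 1.96).

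| Assumed loss | Complete cases | Overall regression test | Correlation, rho = 0.3 |
|---|---|---|---|
| 0% | 100 | 81.4% | 86.2% |
| 5% | 95 | 78.8% | 84.4% |
| 10% | 90 | 76.0% | 82.3% |
| 15% | 85 | 72.8% | 80.0% |
| 20% | 80 | 69.5% | 77.5% |
| 30% | 70 | 61.8% | 71.7% |

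**4. Effect detectable by the overall test at 80% power.** f² is 0.146 at 100 complete cases, 0.163 at 90, 0.185 at 80 and 0.215 at 70. From 97 complete cases downwards it exceeds the medium value of 0.15.

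**5. The single exposure coefficient.** The overall test asks whether all six predictors together explain anything. The study's question concerns the body-measure change, adjusted for the rest. That test has 1 and N − 7 degrees of freedom. With partial f² = 0.15 it needs N = 55, and its power is 97% at 100, 93% at 80, 89% at 70 and 84% at 60 (40% loss). The partial f² detectable at 80% power is 0.080 at N = 100 and 0.116 at N = 70. With partial r = √(f²/(1 + f²)), these are √(0.080/1.080) = 0.27 and √(0.116/1.116) = 0.32.

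**6. Which analyses are exposed.** Body mass change does not depend on attending visit 2 but does lose deleted withdrawals. Composition and questionnaire analyses lose missed visits and withdrawals. Size and shape analyses also lose every off-site participant.

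**The case against.** The strongest reply is that a medium effect of body composition remains detectable. On the test that matches the research question, power at f² = 0.15 is 89% with 70 complete cases and 84% with 60. This stands. A reader might infer from the shortfall that the data could not show a medium composition effect. The documents do not support that: the shortfall belongs to the overall test and, beyond about 15% loss, to the correlations. The reply does not rescue the statement as written, because the protocol sizes on the overall test and does not mention the single coefficient.

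A reader might also infer that the stated power is certain to be missed. That too goes further than the text. The protocol says that data might be missing and gives no rate. At 5% loss the overall test has 79% power, which is a trivial deficit.

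The plan also contains real mitigation: routine weighing for body mass change, which it counts among its key outcomes together with surgical outcomes; off-site sessions that still yield composition and questionnaires; a commitment to convenient appointments; and multiple imputation. These reduce the loss but do not remove it. Imputation is conditional on rejecting MCAR and does not restore the full information, off-site sessions give no scan, and weighing does not bring back deleted withdrawals.

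Finally, the study is observational and describes itself as exploratory, with no single confirmatory test. This lowers the stakes. The power claim is nevertheless explicit and unrestricted, and it sits beside the text that undermines it, so it is more than a detail left to an analysis plan.

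**Conclusion.** The point holds, within limits. The figures 98 and 84 are correct. What fails is the step from them to 100 recruited participants, because 80% power for the six-predictor overall test holds only with at least 98 complete cases and the plan foresees fewer for composition, size and shape, and questionnaire analyses. Overall-test power is 79%, 76%, 69% and 62% at losses of 5%, 10%, 20% and 30%. Those rates are assumptions, since the documents give none. The correlation claim is sturdier and fails only beyond about 15% loss. Body mass change is largely unaffected by missed visits. The consequence is a power statement that is too broad. It does not show that a medium adjusted effect of body composition would go undetected.

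**What to change.** Rewrite the sample size paragraph:

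1. Limit the 80% claim for the overall regression test (f² = 0.15, six predictors) to analyses with at least 98 complete cases, and the correlation claim to analyses with about 84.
2. Give the expected number of complete cases from the Active Together attendance data that the section already cites, allowing for withdrawals, and separately for size and shape, where off-site participants contribute nothing.
3. Give the detectable effect at that number, both for the overall test and for the exposure coefficient adjusted for the planned covariates. With six predictors, the latter is a partial f² of 0.080 at 100 complete cases and 0.116 at 70.
4. Say that body mass change is expected to keep nearly all participants, apart from deleted withdrawals.

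This costs one paragraph and a look at existing attendance records. It needs no extra patients and changes no analysis. The overall-test claim becomes less favourable, but the exposure-coefficient figures show that the study can still detect a medium adjusted effect.

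### The power statement for 100 recruited participants makes no allowance for loss: the regression margin is 2, the correlation margin 16, and the same section foresees possible missing visit 2 data

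*Protocol article*

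**What the plan says.** The sample size paragraph of the Protocol article (Statistics and analysis) gives two calculations. For the regression: "assuming a medium effect size (F^2^=0.15), significance level=0.05, power=0.8 and number of predictors=6, a sample size of 98 is required". For the correlation: "assuming a two-tailed test, a medium effect size (rho=0.3), significance level=0.05 and power=0.8, a sample size of 84 is required". It then concludes: "Therefore, a sample size of 100 participants is required to detect medium effect sizes with acceptable statistical power". It adds that 100 is also about the number of eligible patients available in the study period. The Abstract shows that 100 is an enrolment figure: "This prospective observational study will recruit 100 adults".

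Earlier in the same section, the plan reports that "many patients are unable to attend assessment appointments prior to surgery, often due to short notice of surgery dates", and says that this might leave data missing at visit 2. Body mass change is to be analysed in all participants, because patients are routinely weighed before surgery. For the rest, "analyses including body composition, size and shape, and questionnaire data will be performed on a smaller cohort if some data are missing". Complete-case analysis comes first when covariates such as body composition are missing. Multiple imputation follows only if the data do not look missing completely at random (MCAR).

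Two other sections bear on the evaluable number:
- Under Procedures (Primary data), participants who cannot travel to the research centre are measured off-site. They have bioimpedance and questionnaires but no BOD POD and no 3D body scan.
- Under Ethics and dissemination, a participant who withdraws before visit 2 or surgery has their data removed from the dataset.

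**The concern.** The two calculations give numbers of participants with usable data, and the conclusion applies them to the number recruited. It sets no limit on which analyses have the stated power, although the same section names a group of analyses that may run on fewer people.

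Those analyses are not peripheral. The aim at the end of the Introduction names body composition changes, nutritional status and quality of life. The Introduction also argues that the effect of weight loss may depend on whether fat or muscle is lost, which body mass alone cannot show. If a composition analysis in a reduced cohort finds nothing, a reader who relies on the 80% statement would give that null result more weight than it deserves.

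**Working it through.** **Inputs** (Protocol article, Statistics and analysis). Regression: f² = 0.15, α = 0.05, power 0.80, 6 predictors, stated N = 98. Correlation: two-tailed, ρ = 0.3, α = 0.05, power 0.80, stated N = 84. Recruited: 100. Loss rate: not given, so a range is assumed.

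**Step 1. Reproduce the plan's regression figure.** For the overall F test, df1 = 6, df2 = N − 7, noncentrality λ = f²·N, and power = P(F′ > F₀.₉₅).
- N = 98: λ = 0.15 × 98 = 14.70, critical F(6, 91) = 2.200, power 0.804.
- N = 97: λ = 14.55, power 0.798.

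The smallest N with at least 0.80 is 98, as stated.

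**Step 2. Reproduce the correlation figure.** Fisher z with the small-sample term: power ≈ Φ{[atanh(ρ) + ρ/(2(N − 1)) − atanh(r_c)]·√(N − 3)}, where r_c is the critical correlation.
- N = 84: r_c = 0.2146 and atanh(r_c) = 0.2180. The shifted mean is 0.3113 and √81 = 9. Φ(0.840) = 0.800.

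Plain Fisher z gives 85 and a noncentral t version gives 82, so 84 is sound.

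**Step 3. Margins.** Regression: 100 − 98 = 2, or 2% of those recruited. Correlation: 100 − 84 = 16, or 16%.

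**Step 4. Power and detectable effect after loss.** Same formulas at N = 100 × (1 − loss), and inverted for the effect detectable with 80% power.

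| Assumed loss | N | Regression power (f² = 0.15) | Detectable f² | Correlation power (r = 0.3) | Detectable r |
|---|---|---|---|---|---|
| 0% | 100 | 0.813 | 0.146 | 0.865 | 0.28 |
| 5% | 95 | 0.788 | 0.154 | 0.847 | 0.28 |
| 10% | 90 | 0.760 | 0.163 | 0.827 | 0.29 |
| 20% | 80 | 0.695 | 0.185 | 0.780 | 0.31 |
| 25% | 75 | 0.658 | 0.199 | 0.752 | 0.32 |
| 40% | 60 | 0.532 | 0.255 | 0.653 | 0.35 |

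**Step 5. Which analyses are exposed.**
- Body mass change against surgical outcomes: routine weights protect it from missed visits, but not from the removal of early withdrawals.
- Body composition and visit 2 questionnaires: exposed to missed visits and withdrawals.
- Size and shape: exposed to both, and also absent for every off-site participant by design.

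**The case against.** The strongest reply is that the section deals with this openly. It calls body mass change and surgical outcomes the key outcomes, expects them to be available for everyone, and discloses the smaller cohort for the rest. On that reading the sample size was set for the key analyses. That is a fair account of the intention, but the power sentence carries no such limit.

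A reader might infer that the composition and questionnaire analyses will certainly be underpowered. The documents do not support that. Missing data is worded as something that might occur, no rate is given, and there are efforts to reduce it: convenient appointments, travel reimbursement, a voucher on completing visit 2, and off-site sessions. At 5% loss the shortfall is trivial, and the correlation keeps 80% up to about 16%.

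Other stronger readings also fail:
- The sample size arithmetic is not wrong; both figures reproduce.
- Off-site participants are not lost to body composition, because they have bioimpedance. What they lack is size and shape.
- Nutrition and quality of life do not rest on visit 2 alone. The service collects the same two questionnaires at its own assessments.
- The regression losses shown are for the six-predictor overall test. A single coefficient in that model with f² = 0.15 would keep power 0.911 at N = 75 and 0.838 at N = 60. The plan, however, bases its statement on the overall test.

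Multiple imputation is a partial answer. It is only the fallback, and it would not restore full power where the visit 2 measurement is itself the exposure. The plan also calls the work exploratory and nowhere says that null results will be read as excluding a medium effect, so the risk of over-reading is a caution to readers. Exploratory status does not justify stating a power that the design does not secure.

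**Conclusion.** The point holds in a limited form. The plan claims acceptable power for 100 recruited participants with no allowance for loss, while its own calculations leave a margin of 2 for the regression and 16 for the correlation. The 80% figure is therefore not secured for analyses that need visit 2 composition, size and shape, or questionnaire data. It fails for the six-predictor regression above 2% loss and for the correlation above about 16%.

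How far it falls depends on a loss rate that the documents do not give. Across assumed losses of 5% to 40%, regression power runs from 0.788 to 0.532 and correlation power from 0.847 to 0.653. These figures assume complete-case analysis, the plan's own effect sizes and the six-predictor overall test. The two margins need no assumed loss rate.

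**What to change.** Restate the power sentence in terms of evaluable participants, in two parts.

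1. Limit the 80% statement to body-mass-change analyses against surgical outcomes, at 100 less the withdrawals expected before visit 2 or surgery. It should not be written as holding for all 100: since those participants are removed, three such withdrawals would leave 97 and regression power of 0.798.
2. For analyses that need visit 2 composition, size and shape, or questionnaire data, give power and detectable effect at the complete-case number expected from the Active Together attendance data. For size and shape, also deduct the expected off-site participants. As an illustration only, if 25% were missing: regression power 0.66 with detectable f² 0.20, and correlation power 0.75 with detectable r 0.32.

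No added recruitment is proposed, since the plan describes 100 as about what the period can supply. The cost is a look-up of existing attendance data and a less favourable stated figure.
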